8.2 Causal link between intervention and complication

As a rule, the connection or non-connection of a complication with the intervention performed is obvious. Nevertheless, a distinction is made between safe, probable and unlikely.

8.3 Outcome of the complication

Complications are treated with all available medical means in the interest of patient welfare. However, the outcome of the complication is of secondary importance in the evaluation of this study and is therefore not documented separately (exception: SUE, see 8.4). The severity of the complication sufficiently implies the need for appropriate treatment.

8.4 Definition, reporting and documentation of a serious adverse event (SUE)

Regardless of the documentation of serious or fatal complications, serious adverse events (SUE) must be documented and reported separately.

A serious adverse event (SUE) is any adverse event within the meaning of the serious or fatal complications mentioned in 8.1 that occurs during the course of the study, regardless of the link to the intervention, and has one of the following consequences for the patient

- Death

- Unplanned surgical intervention necessary

- Permanent damage or permanent disability remains

- Unscheduled return to hospital or extended hospital stay: > 10 days

- Unplanned stay intensive care unit: > 1 night

All SUEs must be documented in detail on a special documentation form (notification form "serious adverse event") and reported by fax to the lead study centre in Mannheim within 24 hours, but at least on the next working day after the notification:

Principal investigator (LKP)

University Hospital Heidelberg/Theresienkrankenhaus and St. Hedwigsklinik GmbH

(teaching hospital)

Medical Clinic 1 : Gastroenterology, Oncology and Diabetology

Senior consultant [name]

[name]

[name]

[contact]

[contact]

The SUE form shall contain the following information:

Identification of the study patient, investigator in charge, description of the SUE (event, start and duration, outcome, causal relationship with the intervention, performed

treatment, date and signature of the supervising investigator)

Connection between intervention and Serious Adverse Event (SUE): O secured O probable O possible O unlikely O none O not assessable

Outcome of the Serious Adverse Event:

O Enhancement O Not Yet Restored O Permanent damage O Fatal , cause of death:

O unknown

In the event of an accumulation of or SUEs in a trial centre or trial arm (PTBD or EUCD), the Steering Committee is called in. The Steering Committee reserves the right to draw the appropriate consequences from the reports received, such as the closure of a trial site or termination of the trial.

**9. STATISTICAL METHODS**

In the following, the case number calculation and the statistical evaluation of the most important questions are described. Before the database is closed, the evaluation is defined in detail in a Statistical Analysis Plan (SAP).

9.1 Case Number Calculation

The calculation of the number of cases refers to the primary endpoint, the technical success rate. In the literature, rates of approximately 95% are given in similar studies (Lee et al. (2016)). This is assumed for both groups. If the technical success rate in the PTBD group is less than 10% lower than in the EUCD group, it is considered clinically irrelevant based on clinical judgment. Therefore, the non-inferiority threshold is defined as δ=0.1. At a unilateral significance level of 2.5%, 200 patients (100 per group) are required to perform a Farrington/Manning test at 80% power (calculations with PASS 14.0.8). It is assumed that for a very small proportion of patients the primary endpoint will not be met (for example, if a complication leads to premature discontinuation of the intervention). Therefore, at least 106 patients per group should be included to compensate for a loss of information due to 5% assumed drop-outs.

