| Bapaye 2013 (5) | Retrospective | 26 | 12 (46 %) | Not analyzed | fluoroscopic guidance | only 12/26 (46%) metal stents and 14/26 (54%) external drainages |
| Kashab 2015 (6) | Retrospective | 51 | 20 (39%) | 0,80 (n=41) | no detailed description | Not reported whether metal stents were used or not, many scheduled re- interventions, many bile leaks (n =17) |
| Sharaiha 2016 (7) | Retrospective | 13 | 7 (54%) | 1.70 (n=22) | no detailed description | benign and malignant bile duct obstruction were mixed, number of metal stents remains unclear |
| Lee 2016 (8) | Prospective | 32 | 10 (31%) | 0,93 (n=29) | fluoroscopic guidance | 2 step intervention: external drainage before metal stent insertion, just 15 (48%) of metal stents inserted |
| Sportes 2017 (9) | Retrospective | 20 | 2 (10%) | 1,05 (n=21) | ultrasound guidance | external drain was left after metal stent implantation and removed some days later when stent implantation was clinically successful, scheduled re-interventions were mixed with unscheduled re-interventions |

A comparative study, in which both methods are used and analysed to their best advantage, would require some conceptual changes. On the one hand, PTBD should be used in an optimal way. The following aspects should be considered (10):

1. The primary puncture of the bile duct should not be performed "blind" under radiological fluoroscopy, but under colour contrast Doppler sonographic control, in particular to avoid the puncture of intrahepatic blood vessels (11)

2. The access route of PTBD should preferably be transxyphoidal via the left lobe of the liver, since fewer complications are to be expected here than with the right access route (pain with intercostal position of the drainage, pleural complications) (12).

3. Whenever possible, metal stent-implantation should be performed in the first session and no external or internal/external plastic drainage should remain percutaneous, as this can lead to complications such as an outward or intra-abdominal bile leakage. (10).

4. Endoscopic visual inspection may be helpful in controlling stent release, as it allows precise control of the placement of the distal end of the stent in the duodenal lumen. In biliodigestive anastomosis, endoscopic control is usually not necessary because the stent usually has enough room to unfold and drain bile in the anastomosed loop of the small intestine (10).

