**4. PATIENT AND CENTRE SELECTION**

4.1 Number of patients

According to the case number calculation (Chapter 9.1), 212 patients, i.e. 106 patients per intervention group, are needed to achieve a power of 80% under the assumptions made. Since this is a non-randomised study, in which only one intervention is offered within a centre, recruitment should not be terminated until at least 106 patients have been enrolled in both arms. If the centres belonging to the same intervention arm have together reached the recruitment target of 106 patients, but the centres of the other arm have not yet reached it, recruitment may continue.

The recruitment and treatment of patients will be carried out in the respective study centres. Each centre participating in the study should be able to enrol at least 10 patients within the planned recruitment period of 24 months.

If the total number of cases is not reached by the planned recruitment end (31.01.2020), the recruitment period may be extended if necessary. If recruitment is accelerated, recruitment will be terminated earlier accordingly.

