9.2 Statistical evaluation

The primary endpoint is the technical success rate in malignant distal choledochial stenosis using a self-expanding metal stent. The non-inferiority of PTBD compared to EUCD shall be demonstrated. The corresponding test hypothesis is

H0: pEUCD - pPTBD ≥ δ vs. H1: pEUCD - pPTBD < δ

Where pPTBD describes the technical success rate in the EUCD group, pPTBD the technical success rate in the PTBD group and δ=0.1 the non-inferiority limit.

The non-inferiority of PTBD to EUCD is verified by the Farrington/Manning test with a one-sided significance level of 2.5%.

Since this is a non-inferiority study, the primary evaluation will be based on both the Intention-To-Treat (ITT) Set and the Per-Protocol (PP) Set. In the ITT set, all patients are considered in whom the intervention was performed, even if it was technically unsuccessful or participation in the study was terminated prematurely. If the intervention has to be terminated prematurely (e.g. due to organ perforation), this patient is included in the primary evaluation. The primary evaluation is based on the assumption of technical failure in these patients.

In the PP Set, only those patients are included in the evaluation for whom the intervention was performed and the technical success was measured.

In sensitivity analyses, best case and worst case scenarios are calculated for the missing values. In addition, regression models are planned to investigate the influence of confounders on the endpoints. The variables intervention (EUCD with subgroups or PTBD with side localisation), BMI or bilirubin value are considered as input variables in the baseline study. The binary outcome variable is the technical success of the intervention. The affiliation of the individual patients to the two evaluation collectives is defined in SAP before the database is closed.

If non-inferiority can be shown with regard to the technical success rate, the occurrence of at least one complication (expected complication rate for both interventions: 10-20%) is compared hierarchically in the next step and tested for differences between the groups (based on the ITT set). Due to the hierarchical approach, the full level alpha, in this case two-sided 5%, is tested.

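### Sections 9.1 and 9.2 treat aborted procedures inconsistently, so the stated 80% power is not established for the ITT test at 106 per arm (about 64% to 85%, depending on the reading)

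*Protocol*

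**What the plan says.** Section 9.1 sets out the calculation. On the success rate: "In the literature, rates of approximately 95% are given in similar studies", followed by "This is assumed for both groups". On the margin: "the non-inferiority threshold is defined as δ=0.1". On the result: "At a unilateral significance level of 2.5%, 200 patients (100 per group) are required to perform a Farrington/Manning test at 80% power". It then expects the primary endpoint to be lacking in a very small share of patients, gives as its example an intervention stopped early by a complication, and concludes that "at least 106 patients per group should be included to compensate for a loss of information due to 5% assumed drop-outs".

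Section 4.1 repeats the outcome: "106 patients per intervention group, are needed to achieve a power of 80% under the assumptions made".

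Section 9.2 bases the primary evaluation on both the ITT and the PP set. ITT holds every patient in whom the intervention was performed, and interventions that had to be stopped early are expressly included: "The primary evaluation is based on the assumption of technical failure in these patients". PP holds only patients whose technical success was measured.

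**The concern.** The same event is handled in two ways. In 9.1 an aborted procedure is a lost observation that leaves the success rate at 95% and is made good by six more patients per arm. In 9.2 it is an observed failure that stays in the denominator. Recruiting more patients restores precision lost to missing outcomes, but it does not restore a success rate lowered by extra failures, and a lower rate also means a larger variance.

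At stake is the power of a confirmatory non-inferiority test. That test also decides whether the hierarchical comparison of complications in 9.2 may proceed. If ITT power is well below 80%, a failure to show non-inferiority between truly equal techniques becomes more probable than the protocol tells its readers, and it could be misread as evidence against PTBD.

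**Working it through.** **Inputs.** From 9.1: success p = 0.95 in both arms, true difference 0, margin δ = 0.10, one-sided α = 2.5%, target power 80%, Farrington/Manning test, drop-out 5%. From 4.1: 106 per arm. From 9.2: aborted procedures count as failures in ITT.

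**Formula.** With equal true rates and n per arm,

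power = Φ[(δ√n − 1.960·S0) / S1]

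where S1 = √[2p(1−p)] and S0 = √[a(1−a) + b(1−b)]. Here a and b are the restricted maximum-likelihood rates for PTBD and EUCD under b − a = δ. Exact power sums the binomial probabilities of all outcomes that the test rejects.

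**The plan's own figures.** At p = 0.95, the restricted rates are a = 0.870 and b = 0.970, so S0 = 0.3764 and S1 = 0.3082.
- Sample size: n = (1.960 × 0.3764 + 0.8416 × 0.3082)² / 0.10² = 99.4, so 100 per arm.
- Power at 100: Φ[(1.0000 − 0.7377)/0.3082] = Φ(0.851) = 80.3% (exact 83.2%).
- Inflation: 100/0.95 = 105.3, so 106.

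The plan's arithmetic is correct.

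**ITT power at 106 per arm under each reading** (δ√106 = 1.0296). Let q be the proportion aborted. If 95% applies to completed procedures, the ITT rate is 0.95 × (1 − q).

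| Reading | ITT rate | S0 | S1 | Asymptotic | Exact |
|---|---|---|---|---|---|
| 95% already counts aborted procedures as failures | 95% | 0.3764 | 0.3082 | 82.8% | 84.7% |
| 95% among completed, q = 2% | 93.1% | 0.4059 | 0.3584 | 74.3% | 76.3% |
| 95% among completed, q = 5% | 90.25% | 0.4483 | 0.4195 | 64.0% | 66.1% |

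The last row in full: Φ[(1.0296 − 1.960 × 0.4483)/0.4195] = Φ(0.360) = 64.0%.

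**A mixed case.** Suppose about half of the six extra patients per arm are never treated, so fall outside ITT, and the rest are aborted. Then n = 103, the rate is 95/103 = 92.2%, and power is 69.5% asymptotic, 71.4% exact.

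**Size needed for 80% at 90.25%.** About 152 per arm by the asymptotic formula, about 148 by exact calculation.

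**PP set.** If aborted patients drop out of PP, 106 × 0.95 = 100.7 remain per arm. At 95% success, power there stays at about 80% by the asymptotic formula.

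**The case against.** The strongest reply is that the 95% is already the right rate. Section 9.1 says that the calculation concerns the primary endpoint, and section 2 defines that endpoint as successful implantation of a metal stent. An aborted procedure has no stent and is a failure by definition, so multiplying by 0.95 again would count the same failures twice. Aborted procedures are also only an example in 9.1. Section 4.6.1 allows withdrawal, and 9.2 plans best-case and worst-case analyses for missing values, so part of the 5% may be truly missing outcomes. Finally, the inflation has a use in PP, where it keeps about 100 evaluable patients per arm.

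Much of this stands. A reader might infer that ITT success simply is about 90% and power about 66%. The documents do not support that as a fact, because both conditions behind it are left open. But the reply does not rescue 9.1 as written. If 95% is the ITT rate, the six extra patients repair nothing in ITT for the only cause named. And 95% in ITT with the whole 5% aborted would leave almost no failures among completed procedures. Adequate power in PP does not help if ITT must also succeed.

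A reader might also infer from Table 1 in section 1.1 that the study cited for 95% cannot support it for PTBD, since the table notes "just 15 (48%) of metal stents inserted". Table 1 gives neither that study's technical success rate nor its definition of success, and the protocol plans an optimised PTBD technique. The table does not show that the 95% is unsupported.

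**Conclusion.** The inconsistency between 9.1 and 9.2 is real. The plan's arithmetic is right, but the 80% is not established for the ITT test. At 106 per arm, with equal true success rates, ITT power lies between about 64% and 85%. The lower end (64% asymptotic, 66% exact) needs two assumptions: 95% is the rate among completed procedures only, and all of the 5% are aborted procedures. The upper end (83% to 85%) needs the 95% to count aborted procedures as failures already and all 106 patients to be analysed. The protocol settles none of these.

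Nor do the figures show that the design makes an inconclusive result likely. Even at the low end, and with equal techniques, the ITT test would succeed about two times in three.

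**What to change.** In section 9.1, and in the matching sentence of 4.1, state whether the 95% is the ITT success rate with aborted procedures counted as failures.

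- If it is, remove aborted procedures as the example of a drop-out and reserve the 5% allowance for outcomes that are truly missing.
- If it is not, give the expected proportion aborted, base the calculation on the resulting ITT rate, and restate ITT power at 106 per arm. That power could be as low as about 64% to 66%.

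In either case, say which analysis set the quoted power refers to. The cost is a few sentences and possibly a less favourable stated power. No change in enrolment is needed, provided the lower power is stated openly.

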9.2 Statistical evaluation

The primary endpoint is the technical success rate in malignant distal choledochial stenosis using a self-expanding metal stent. The non-inferiority of PTBD compared to EUCD shall be demonstrated. The corresponding test hypothesis is

H0: pEUCD - pPTBD ≥ δ vs. H1: pEUCD - pPTBD < δ

Where pPTBD describes the technical success rate in the EUCD group, pPTBD the technical success rate in the PTBD group and δ=0.1 the non-inferiority limit.

The non-inferiority of PTBD to EUCD is verified by the Farrington/Manning test with a one-sided significance level of 2.5%.

Since this is a non-inferiority study, the primary evaluation will be based on both the Intention-To-Treat (ITT) Set and the Per-Protocol (PP) Set. In the ITT set, all patients are considered in whom the intervention was performed, even if it was technically unsuccessful or participation in the study was terminated prematurely. If the intervention has to be terminated prematurely (e.g. due to organ perforation), this patient is included in the primary evaluation. The primary evaluation is based on the assumption of technical failure in these patients.

In the PP Set, only those patients are included in the evaluation for whom the intervention was performed and the technical success was measured.

In sensitivity analyses, best case and worst case scenarios are calculated for the missing values. In addition, regression models are planned to investigate the influence of confounders on the endpoints. The variables intervention (EUCD with subgroups or PTBD with side localisation), BMI or bilirubin value are considered as input variables in the baseline study. The binary outcome variable is the technical success of the intervention. The affiliation of the individual patients to the two evaluation collectives is defined in SAP before the database is closed.

If non-inferiority can be shown with regard to the technical success rate, the occurrence of at least one complication (expected complication rate for both interventions: 10-20%) is compared hierarchically in the next step and tested for differences between the groups (based on the ITT set). Due to the hierarchical approach, the full level alpha, in this case two-sided 5%, is tested.

The evaluation of further secondary endpoints is done in the ITT set. With regard to the complication rate, PTCD is expected to have a lower complication rate than EUCD. No missing values are implanted during the evaluation of secondary endpoints. The evaluation is purely descriptive. Appropriate statistical methods are used according to the underlying distribution. For continuous endpoints, the mean, standard deviation, median, interquartile distance, and minimum and maximum are reported separately and in total for the two groups. For categorical endpoints, absolute and relative frequencies are given, also separately for the two groups and in total. Event times are displayed and evaluated using survival time analysis methods (e.g. Kaplan Meier). Descriptive p-values are given together with 95% confidence intervals. In the EUCD group, descriptive p-values are also divided by method (see 5.1). In addition, unless defined in the secondary endpoints, adverse events are evaluated and compared.

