6.1 Screening visit

A paper-bound explanation of the study (own form) for the intervention (commercial form) and the sedation or anaesthesia (commercial form) of the patient is provided. Each potential study patient will receive a CT or MRI abdomen in addition to an abdominal sonography. The inclusion and exclusion criteria are checked (Case Report Form , p.2). Every patient who has been positively screened is included in the study if written consent is obtained (Case Report Form, p. 1). In the case of patients who are still capable of giving birth, a possible pregnancy is excluded by pregnancy tests.

It is assumed that almost all positively "screened" patients want to undergo an intervention under study conditions. In this situation, surgery is usually either not possible (pre-operated abdomen, advanced tumour disease) or is associated with a considerable risk. The performance of a PTBD/EUCD is therefore mostly without alternative. The screening list lists (separate form) which patients have been screened positively (inclusion and exclusion criteria fulfilled). Should a patient not be included in the study (e.g. because of refusal to participate in the study), this is briefly explained.

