**8. ASSESSMENT OF PATIENT SAFETY**

8.1 Definition and documentation of complications

In the study population with advanced oncological diseases, numerous tumour- and tumour therapy-related adverse events are to be expected.

For the assessment of patient safety with regard to the interventions performed in the study, only certain adverse events in terms of potential complications of PTBD/EUCD, of which a major part is to be expected within a period of 30 days after the intervention, are of interest and complications are to be documented in the notification form.

The following potential complications of PTBD and/or EUCD are recorded in the CRF with date and severity (mild, moderate, severe, fatal) (see Table 1, below) (multiple entries possible):

- Bleeding/haematoma

- Haemobilia

- intra-abdominal bile leakage

- Pneumothorax

- Biliary pleural effusion

- Pneumoperitoneum

- Perforation of the gastrointestinal tract

- Therapy-relevant (cholangial-)sepsis

- Newly occurring cholangitis (see comment below)

- Abscess

- Purulent peritonitis

- Cholecystitis

- Metal stent dysfunction/migration

- Other (description in free text)

To be distinguished from the above mentioned complications and not to be recorded:

- metal stent-closure caused by the ingrowth of tumour tissue or by choledocholithiasis

- Adverse events associated with anaesthesia and/or sedation

- Adverse events associated with chemotherapy

- Cholangitis as a possible complication of the intervention by PTBD or EUCD requires a special consideration: Only the newly appeared and not the pre-existing cholangitis is considered a complication ! Since the patients are treated peri-procedurally prophylactically with antibiotics, cholangitis is only considered a complication if an intensification of antibiotic therapy becomes necessary and the cholangitis can be safely attributed to the intervention !

- Postinterventional pain (will be collected separately)

Severity of the complication

Table 1: Severity of complications according to the recommendations of the American Society for Gastrointestinal Endoscopy (ASGE) (16,17)

| **Severity of the complication** | **Slightly** | **Moderate** | **Severe** | **Fatal** |
| --- | --- | --- | --- | --- |
| Procedure aborted or not yet started because of UE | x |  |  |  |
| Unscheduled anesthesiological measure required in connection with a procedural adverse event (e.g. endotracheal intubation) |  | x |  |  |

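### The set called ITT is a treated-only set: enrolled patients whose procedure is never started fall outside both primary analyses

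*Protocol*

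**What the plan says.** Enrolment comes before the procedure. Section 6.1 states: "Every patient who has been positively screened is included in the study if written consent is obtained". Section 11.3 requires consent before the first intervention. Section 4.2 allows one technique per centre, so a patient's arm is known at enrolment.

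Section 9.2 says that "the primary evaluation will be based on both the Intention-To-Treat (ITT) Set and the Per-Protocol (PP) Set". The first set is defined by "In the ITT set, all patients are considered in whom the intervention was performed", and the sentence continues: "even if it was technically unsuccessful or participation in the study was terminated prematurely". Aborted procedures are covered explicitly: "If the intervention has to be terminated prematurely (e.g. due to organ perforation), this patient is included in the primary evaluation". For their outcome, "The primary evaluation is based on the assumption of technical failure in these patients". In the per-protocol set, "only those patients are included in the evaluation for whom the intervention was performed and the technical success was measured".

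The severity table in 8.1 has a row reading "Procedure aborted or not yet started because of UE". Section 9.2 deals with the aborted half of that row and is silent on the half that was not started. The word performed is not defined. Section 9.2 leaves to the SAP which individual patients belong to which set.

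**The concern.** An intention-to-treat set should contain every enrolled patient under the technique intended for that patient. Here the intended technique is fixed by the centre at consent, but the set begins only when the intervention is performed. The per-protocol set carries the same condition and adds only that technical success was measured. The two primary analyses therefore share one blind spot, and agreement between them says nothing about it.

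This matters because the reasons for not starting can depend on the technique. Section 5.1 describes PTBD as needing an ultrasound-guided percutaneous route at a safe distance from neighbouring structures. For EUCD it offers several access routes and fallback methods. If more PTBD patients turn out to be unsuitable after consent, leaving them out raises the PTBD success rate relative to EUCD and favours the non-inferiority claim. The trial is open and non-randomised, so neither blinding nor randomisation limits selective exclusion after enrolment. The best-case and worst-case analyses in 9.2 are for missing values. Nothing extends them to patients outside both sets.

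**Working it through.** **Inputs from the protocol (9.1, 9.2).** Success is 95% in both arms, the margin is δ = 0.10, the one-sided level is 2.5%, the test is Farrington/Manning, and the size is 100 per group, or 106 after 5% drop-out.

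**Assumption.** The number k of enrolled PTBD patients whose procedure is never started is not given. It is varied from 0 to 5 of 106, with none in EUCD.

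**1. Reproduce the stated sample size.** With p₁ = EUCD and p₂ = PTBD, the rates restricted to a difference of 0.10 are 0.9703 and 0.8703.

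- s₀ = √(0.9703×0.0297 + 0.8703×0.1297) = 0.3764
- s₁ = √(2×0.95×0.05) = 0.3082
- n = [(1.960×0.3764 + 0.8416×0.3082)/0.10]² = 99.4, so 100 per group
- 100/0.95 = 105.3, so 106 per group

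The plan's figures reproduce. Power at 106 per group is 82.8% (84.7% by exact enumeration). These figures do not depend on the point at issue.

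**2. Error from leaving out unstarted patients.** Suppose the all-enrolled truth sits on the margin: EUCD 0.95, PTBD 0.85 with unstarted cases counted as failures. A correct test should then claim non-inferiority 2.5% of the time. In the treated-only set the PTBD rate becomes

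p₂ = 0.85 × 106/(106 − k)

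and the chance of claiming non-inferiority is

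Φ{[(δ − (0.95 − p₂))·√106 − 1.960·s₀]/s₁},

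with s₀ from the restricted rates and s₁ from 0.95 and p₂. For simplicity n stays at 106 in both arms.

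For k = 2: p₂ = 0.8663, the difference is 0.0837, s₀ = 0.4101 and s₁ = 0.4041. The argument is (0.0163×10.296 − 1.960×0.4101)/0.4041 ≈ −1.57, which gives 5.8%.

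| Unstarted PTBD patients (k of 106) | Treated-only PTBD rate | Apparent difference | Chance of claiming non-inferiority |
| --- | --- | --- | --- |
| 0 | 85.0% | 10.0 points | 2.5% |
| 1 | 85.8% | 9.2 points | 3.8% |
| 2 | 86.6% | 8.4 points | 5.8% |
| 3 | 87.5% | 7.5 points | 8.6% |
| 5 | 89.2% | 5.8 points | 18% |

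Exact enumeration at 106 per arm, with shares of 1%, 2%, 3% and 5% in place of counts, gives 3.7%, 5.8%, 9.0% and 19.8%, against 2.3% with none. The two methods agree closely.

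**3. Power of an all-enrolled analysis.** Take 95% success among treated patients, 106 per arm, and unstarted patients counted as failures. With one unstarted patient in each arm, success is 0.95×105/106 = 94.1% and power is 78.6%. With three in each arm, success is 0.95×103/106 = 92.3% and power is 71.2%. With none, power stays at 82.8%.

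**The case against.** The strongest reply is that the plan already handles what matters. A reader who stops at the word performed might infer that technique-related failures are removed from the primary analysis. The documents do not support that: the same sentence keeps technically unsuccessful patients, and the next two keep aborted procedures as failures. This part of the objection stands in full for every failure after the procedure has begun.

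The remaining group is probably small. Sonography and CT or MRI are required for inclusion, partly to plan the intervention (4.4). Baseline should be the day before the procedure (6.2), and 6.1 regards the intervention as mostly without alternative. The row in 8.1 grades severity. It shows that a procedure not started is conceivable, but not that it is common or differs between arms. All of this limits the likely size without closing the gap.

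A reader might also infer that the trial is badly underpowered. With five unstarted patients in PTBD only, an all-enrolled analysis would have 29% power. That figure describes the proposed analysis under an assumed count and is not a defect of the present plan. The protocol ties its 5% drop-out to loss of the endpoint, and does not attribute it to unstarted procedures.

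It can be said that without randomisation there is no randomised comparison for ITT to protect. That is true, but the choice of who is counted after enrolment can still bias the comparison. Finally, the SAP may settle borderline cases. It would be applying a definition that the protocol has already fixed, and that definition excludes unstarted patients.

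**Conclusion.** The point holds in a limited form. The set called ITT is a treated set, the per-protocol set shares its restriction, and no stated primary analysis covers all enrolled patients. The possible harm is a false claim of non-inferiority. Two unstarted PTBD patients would more than double the nominal one-sided error (2.5% to 5.8%), and five would bring it to about 18%.

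These sizes rest on three assumptions: truth exactly at the margin, unstarted cases in PTBD only, and counts that the protocol does not supply. With no such cases there is no effect. Cases occurring equally in both arms would produce less bias than the table shows. The correction is worth making because it is cheap and the design has no other safeguard on this point.

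**What to change.** Amend section 9.2 as follows.

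- Define the ITT set as all enrolled, eligible patients, analysed by the enrolling centre's technique.
- Count a procedure not started for technique- or event-related reasons as a technical failure. Aborted procedures are already counted so.
- Define performed as any attempt begun.
- Keep the present set, renamed treated set, as a supportive analysis.
- Handle withdrawal of consent before the procedure in a sensitivity analysis.
- Report unstarted cases with their reasons, by arm.

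The cost is one paragraph. If such cases occur, the observed success rate falls and power falls with it: from 82.8% to 78.6% with one per arm and to 71.2% with three per arm, under the assumptions above. If none occur, nothing changes.
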